**Fig. 1 Fig1:**
[figure not shown]
Ideal timeline of CIFRA study

Atropine 0.25 mg sub cutis will be administered for the prevention of acute cholinergic events before irinotecan infusion. Premedication with *antihistamines at standard doses and* dexamethasone 4 mg will be applied before cetuximab infusion.

### Duration of therapy

Administration of folfiri/cetuximab will be allowed until progression or unacceptable toxicity. In case of unacceptable toxicity related to irinotecan the patients will continue cetuximab and 5-FU until progression. In case of unacceptable toxicity related to cetuximab the patient will continue folfiri until progression. In case of unacceptable toxicity related to 5-FU the patients will continue with cetuximab and irinotecan until progression.

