### Dose modifications for folfiri

Dose reductions wil be applied in relation to the more severe side effect. Once modified, the dose of the drug will be the same for the subsequent cycles. A 20% reduction of folfiri will be permitted in case of grade ≥ 3 of haematologic or non-haematologic toxicities (except for alopecia). Folfiri will be rechallenged after *recovery* of toxicity to baseline or *grade 1* or less. At the second appearance of grade ≥ 3 side effects a dose reduction of 50% will be applied; after a further grade ≥ 3 toxicity or after the first appearance of grade ≥ 2 cardio-vascular chemotherapy will be permanently discontinued. Chemotherapy will also be interrupted in case of postponement of the administration for more than 4 weeks. No prophylactic use of G-CSF o erythropoetin is planned.

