### Dose modifications for cetuximab

Cetuximab infusion will be delayed in case of grade > 3 cutaneous toxicity for 2 weeks. The investigator will also consider the administration of topical and/or oral antibiotic drugs and/or topical corticosteroids [30]. The treatment will be reintroduced if the cutaneous toxicity reduces to grade 2 or lower. If grade 3 skin toxicity reoccurs at a second or third time, cetuximab will be postponed for a further 2 weeks, but when reintroduced the dose will be reduced to 200 mg/mq and 150 mg/mq, respectively. Dose reductions of cetuximab are permanent and it will be permanently discontinued in case of 4 weeks suspension or fourth grade 3 toxicity event occurrence despite appropriate dose adjustments. Allergic reactions may occur during or after administration of cetuximab. In case of allergic reaction, the patient will be treated according to clinical practice. The patient should also be asked to report immediately to the doctor if any late reaction occurs. In case of grade 1 allergic reaction the cetuximab infusion rate will be reduced at 50%; it will not be increased subsequently, but rather reduced at any subsequent administration. In case of a second allergic or hypersensitive reaction despite the reduced infusion rate, the infusion will be interrupted and the patient will continue with folfiri alone. If the patient experiences an allergic or hypersensitive reaction of grade > 3, cetuximab will be permanently discontinued and chemotherapy will be continued if considered appropriate by the investigator.

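### When toxicity is attributed to one chemotherapy drug, two sections of the protocol can give opposite instructions for the other drug

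*Protocol article*

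**What the plan says.** Three neighbouring sections of the protocol article govern what happens after toxicity.

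- **Duration of therapy** removes only the responsible drug. For irinotecan: "In case of unacceptable toxicity related to irinotecan the patients will continue cetuximab and 5-FU until progression". For 5-FU: "In case of unacceptable toxicity related to 5-FU the patients will continue with cetuximab and irinotecan until progression". For cetuximab: "In case of unacceptable toxicity related to cetuximab the patient will continue folfiri until progression".
- **Dose modifications for folfiri** acts on the combination. Folfiri is reduced by 20% at the first grade ≥ 3 toxicity and by 50% at the second. After a further one, or after a first grade ≥ 2 cardiovascular event, "chemotherapy will be permanently discontinued". A delay is handled in the same unit: "Chemotherapy will also be interrupted in case of postponement of the administration for more than 4 weeks".
- **Dose modifications for cetuximab** has two clauses on chemotherapy after an allergic reaction. After a second reaction despite a slower infusion, "the infusion will be interrupted and the patient will continue with folfiri alone". After a reaction of grade > 3, "cetuximab will be permanently discontinued and chemotherapy will be continued if considered appropriate by the investigator".

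**The concern.** The first two sections differ in what they act on. One asks which drug caused the toxicity and keeps the rest of the regimen going. The other counts events by grade, does not ask about cause, and ends chemotherapy as a whole. Neither refers to the other or says which takes precedence.

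Two clinicians following the same text could therefore treat the same patient differently after the same event, which is a safety matter. It also affects the analysis. Study design and statistical analyses commits to summarising dose changes, interruptions, treatment duration and the reasons for protocol deviations. Where two stated rules compete, an action that complies with one section is a deviation under the other, so those summaries would depend on which section was consulted.

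**Working it through.** No arithmetic settles this point. The check is to take specific events and read off what each section instructs.

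**Irinotecan and 5-FU**

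| Event | Duration of therapy | Dose modifications for folfiri | Result |
|---|---|---|---|
| Third grade ≥ 3 toxicity, attributed to irinotecan, regarded as unacceptable | Irinotecan stops; 5-FU and cetuximab continue | All chemotherapy stops permanently | Opposite instructions for 5-FU |
| First grade ≥ 2 cardiovascular event, attributed to 5-FU, regarded as unacceptable | 5-FU stops; irinotecan and cetuximab continue | All chemotherapy stops permanently | Opposite instructions for irinotecan |
| Third grade ≥ 3 toxicity, not attributable to one drug | No rule is triggered | All chemotherapy stops permanently | No conflict |
| Grade 2 cardiovascular event, not regarded as unacceptable | No rule is triggered | All chemotherapy stops permanently | No conflict |

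The conflict therefore needs two conditions: attribution to a single agent, and the event counting as unacceptable toxicity. The second is the natural reading of an event that leads to permanent discontinuation, but the article does not say so.

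Could *chemotherapy* in the folfiri section mean only the responsible drug? The surrounding text points the other way. The reductions and the rechallenge in that section are stated for folfiri. Elsewhere the article applies the term to doublets (The current therapeutic context of mCRC and CIFRA hypothesis) and treats irinotecan as one component of a chemotherapy administration (Therapeutic schedule). One sentence in the folfiri section does speak of the dose of a single drug, which leaves the unit of action unclear.

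**Cetuximab**

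| Event | Duration of therapy | Dose modifications for cetuximab | Result |
|---|---|---|---|
| Second allergic reaction despite reduced infusion rate | Folfiri continues | Folfiri continues | Agreement |
| Allergic reaction of grade > 3 | Folfiri continues, no exception named | Chemotherapy continues at the investigator's discretion | Different, unless the second clause is an exception |

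**Size.** The document gives no frequency for a third grade ≥ 3 event, for grade ≥ 2 cardiovascular events or for attribution to one agent. For context only, Previous results of folfiri plus cetuximab cites grade 3–4 haematologic toxicity in 25% and diarrhoea in 11% of patients in the phase III comparison with folfiri plus bevacizumab. In 34 patients that would be 0.25 × 34 = 8.5 and 0.11 × 34 = 3.7. These figures describe patients with any such toxicity, not a third event, so they show that the first step of the ladder will be reached but do not estimate how many patients meet the conflict.

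**The case against.** The strongest reply is that these are general and specific rules that can work together. The drug-by-drug rule would apply where one agent is clearly responsible, and the block rule to repeated or unattributed toxicity on the combination. *Unacceptable toxicity* is undefined, so nothing forces the triggers in the folfiri section to fall under it, and Duration of therapy does not mention cardiovascular events. End-of-treatment phase also allows suspension for toxicity or at the patient's request, so the instruction to continue is not absolute. Finally, the article condenses a full protocol that may define the term.

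Part of this stands. The conflict is conditional, and a reader who inferred that every third grade ≥ 3 event or every grade ≥ 2 cardiovascular event has two mandated outcomes would go too far; the table shows cases without conflict. The missing definition is not itself the point, since an article may leave it to the full protocol. But the proposed division of labour is not written anywhere. The folfiri section has no exception for an event attributed to one drug, and the general permission to suspend treatment does not say which drug it concerns. What remains is a clash between rules that the article does state.

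On cetuximab the reply is stronger. A reader might infer that continuing folfiri is mandatory in one place and discretionary in another across the board. The text does not support that: the discretion covers only allergic reactions of grade > 3, and the adjacent clause agrees with Duration of therapy. An intended exception is the natural reading.

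A reader might also infer damage to the primary endpoint. That is not shown. Under the block rule, the grade ≥ 3 route to stopping comes only after two earlier events and two reductions, and response is first assessed at 3 months, so many such cases could arise after a response is recorded. The document gives no timing either way.

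**Conclusion.** The point holds in conditional form. For an event that meets a stopping trigger in the folfiri section, is attributed to irinotecan or 5-FU alone, and is regarded as unacceptable toxicity, the protocol both continues and permanently stops the other chemotherapy drug. The consequences are for patient safety and for the classification of protocol deviations. Treatment exposure may differ too, and through it response, response duration and PFS could be affected, but the documents do not establish such an effect. The two-stage boundaries (more than 6 responses in 14 patients, more than 18 in 34) do not depend on it. The number of patients concerned cannot be derived.

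The cetuximab clause is a minor, separate matter of cross-referencing. The whole point is worth correcting but does not threaten the design.

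**What to change.** Reconcile Duration of therapy with Dose modifications for folfiri. For each stopping trigger in the latter, state whether it acts on the responsible drug or on all chemotherapy, and which section governs when the event is attributed to one agent. If the discretion after allergic reactions of grade > 3 is an intended exception, refer to it in Duration of therapy. The clinical team decides which rule applies; this review takes no position on that. The deviation summaries should then be classified against the reconciled text.

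The cost is a clarifying amendment. Sample size, decision boundaries and analysis methods stay as they are.

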### Dose modifications for folfiri

Dose reductions wil be applied in relation to the more severe side effect. Once modified, the dose of the drug will be the same for the subsequent cycles. A 20% reduction of folfiri will be permitted in case of grade ≥ 3 of haematologic or non-haematologic toxicities (except for alopecia). Folfiri will be rechallenged after *recovery* of toxicity to baseline or *grade 1* or less. At the second appearance of grade ≥ 3 side effects a dose reduction of 50% will be applied; after a further grade ≥ 3 toxicity or after the first appearance of grade ≥ 2 cardio-vascular chemotherapy will be permanently discontinued. Chemotherapy will also be interrupted in case of postponement of the administration for more than 4 weeks. No prophylactic use of G-CSF o erythropoetin is planned.

### Dose modifications for cetuximab

Cetuximab infusion will be delayed in case of grade > 3 cutaneous toxicity for 2 weeks. The investigator will also consider the administration of topical and/or oral antibiotic drugs and/or topical corticosteroids [30]. The treatment will be reintroduced if the cutaneous toxicity reduces to grade 2 or lower. If grade 3 skin toxicity reoccurs at a second or third time, cetuximab will be postponed for a further 2 weeks, but when reintroduced the dose will be reduced to 200 mg/mq and 150 mg/mq, respectively. Dose reductions of cetuximab are permanent and it will be permanently discontinued in case of 4 weeks suspension or fourth grade 3 toxicity event occurrence despite appropriate dose adjustments. Allergic reactions may occur during or after administration of cetuximab. In case of allergic reaction, the patient will be treated according to clinical practice. The patient should also be asked to report immediately to the doctor if any late reaction occurs. In case of grade 1 allergic reaction the cetuximab infusion rate will be reduced at 50%; it will not be increased subsequently, but rather reduced at any subsequent administration. In case of a second allergic or hypersensitive reaction despite the reduced infusion rate, the infusion will be interrupted and the patient will continue with folfiri alone. If the patient experiences an allergic or hypersensitive reaction of grade > 3, cetuximab will be permanently discontinued and chemotherapy will be continued if considered appropriate by the investigator.

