### Therapeutic schedule

The therapeutic schedule [22, 23] is represented by cetuximab 400 mg/mq intravenously (iv) with a loading dose of 400 mg/mq at the first cycle followed by 250 mg/mq iv weekly. Cetuximab will be diluted in 500 ml of saline solution and administered by iv infusion in 90 min. The administration of irinotecan will precede that of cetuximab and will consist on a dose of 180 mg/mq diluted in 500 ml of saline solution and administered iv in 60 min. Fluorouracil (5-FU) will be administered at a dose of 400 mg/mq in slow iv bolus at half of lederfolin 200 mg/mq (diluted in 250 ml of saline solution) 2-h infusion. An elastomeric pump with 5-fu 2400 mg/mq in continuous 46 h-infusion will be adminstered after lederfolin. The therapeutic scheme just described is briefly indicated as folfiri/cetuximab. Only at the first administration of CT, irinotecan will not be administered (Fig. 1). This is a peculiar and innovative characteristic of the CIFRA study. ADCC occurs rapidly at the beginning of the therapy because it involves lympocytes subpopulatons (i.e. NK) that do not require immunological priming. Although immunomodulatory effects of irinotecan are not described, it is reasonable and biologically plausible that irinotecan-induced lymphopenia could interfere the ADCC phenomena.

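### The 2-week cetuximab hold for skin toxicity is triggered at grade > 3, but the ladder that follows counts grade 3 events; the trigger should read grade ≥ 3

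*Protocol article*

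**What the plan says.** All the skin-toxicity steps for cetuximab stand in one paragraph of the protocol article, under Dose modifications for cetuximab:

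- Hold: "Cetuximab infusion will be delayed in case of grade > 3 cutaneous toxicity for 2 weeks".
- Restart: "The treatment will be reintroduced if the cutaneous toxicity reduces to grade 2 or lower".
- Second and third events: "If grade 3 skin toxicity reoccurs at a second or third time, cetuximab will be postponed for a further 2 weeks", and "when reintroduced the dose will be reduced to 200 mg/mq and 150 mg/mq, respectively".
- Permanent stop: "it will be permanently discontinued in case of 4 weeks suspension or fourth grade 3 toxicity event occurrence despite appropriate dose adjustments".

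Two neighbouring sections bear on the reading. Duration of therapy has a general rule: "In case of unacceptable toxicity related to cetuximab the patient will continue folfiri until progression". Dose modifications for folfiri sets its own trigger with a different sign: "A 20% reduction of folfiri will be permitted in case of grade ≥ 3 of haematologic or non-haematologic toxicities".

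**The concern.** The hold is set one grade above the events that the rest of the paragraph counts. A patient with a first grade 3 skin event does not meet the hold criterion. That same event must nevertheless be number one if later events are to be the second, third and fourth.

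This is a threshold that investigators act on. As written, a hold at a first grade 3 skin event is neither required nor forbidden. Two patients with the same event could therefore be managed differently, both within protocol. It is also less clear which event starts the count leading to permanent dose reductions and then to permanent discontinuation. The section Study design and statistical analyses promises summaries of dose changes, interruptions and reasons for protocol deviation. Those summaries are easier to interpret if one unambiguous hold rule stands behind them.

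**Working it through.** The plan gives no figure to reproduce here, so the check is a logical one: take each grade and occurrence and see which action the text requires.

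**Inputs.** The hold, restart, second/third-event and stopping rules are those quoted above from Dose modifications for cetuximab. The grading scale is in Response and toxicity assessment, where grade 5 is death, so in a living patient a grade above 3 is grade 4. The maintenance dose is in Therapeutic schedule: "followed by 250 mg/mq iv weekly".

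**Step 1: the ladder as written and as corrected.**

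| Skin event | As written | With grade ≥ 3 throughout |
|---|---|---|
| First grade 3 | No mandated action (3 is not > 3) | 2-week delay; restart at grade ≤ 2; no reduction stated |
| Second grade 3 | Another 2-week delay, then 200 mg/mq | Same |
| Third grade 3 | Another 2-week delay, then 150 mg/mq | Same |
| Fourth grade 3 | Permanent stop | Same |
| Any grade 4 | 2-week delay; restart at grade ≤ 2; permanent stop at 4 weeks; restart dose after a recurrence not stated | Counted on the same ladder |

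**Step 2: where the written version conflicts with itself.**

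1. Restart needs grade 2 or lower. Grade 3 is thus too severe to restart on, yet not severe enough to hold for.
2. The second and third grade 3 events are described as recurrences that lead to an additional postponement. Both ideas require an earlier grade 3 event that was itself held.
3. The stop is at the fourth grade 3 event. Events two to four have actions, and event one has none.

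Replacing > with ≥ in the hold rule removes all three conflicts.

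**Step 3: is the gap filled elsewhere?** The rule in Duration of therapy names no grade and moves the patient to folfiri alone, which is different from a 2-week delay. The rule in Dose modifications for folfiri governs the chemotherapy doses only. Neither supplies a hold for a first grade 3 skin event.

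**Step 4: could the sign have been lost in text extraction?** This is unlikely. The ≥ sign survives in the adjacent folfiri section.

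**Step 5: scale.** The section on previous results of folfiri plus cetuximab quotes 26% grade 3–4 skin reactions in an earlier phase III trial. Assuming that rate holds here, 0.26 × 34 = 8.84, or about 9 of the 34 planned patients. The article does not split grade 3 from grade 4. For one patient on the maintenance dose, a 2-week hold covers two weekly doses: 2 × 250 = 500 mg/mq. That amount would be held under the corrected rule and is not required to be held under the written one.

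**The case against.** The best case against is that the paragraph nearly corrects itself. The references to recurrence, to an additional delay and to a restart at grade 2 or lower leave one workable reading, and an experienced oncologist would probably hold at a first grade 3 event. The trial is single-arm and single-centre, so no imbalance between arms or sites can follow. This stands as a limit on the consequences. It does not make the stated threshold right: a dose-hold rule should not have to be inferred from the steps after it. Nor is this a detail that a condensed article may leave out, because the article states the threshold and then contradicts it.

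The comparison with the folfiri trigger is only supporting evidence. That rule concerns other drugs, a reduction that is permitted rather than required, and a different recovery threshold. The case rests on the cetuximab paragraph alone.

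Four stronger readings are tempting and are not supported:

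- A reader might infer that the protocol requires full-dose cetuximab to continue through a first grade 3 event. It does not; it is silent on a hold.
- A reader might infer that recurrent grade 4 skin toxicity is not handled. As written, any grade 4 skin event triggers the delay, the restart condition and the 4-week stop. Only the dose on restart after a recurrence is unstated.
- A reader might take the 9 of 34 as patients who would be misdosed. It is an expected number with a grade 3–4 event under a borrowed rate. How many would be dosed differently depends on investigator behaviour, which the article does not give.
- A reader might infer that the > 3 sign in the allergic-reaction rule of the same section is the same slip. No counted ladder contradicts it there, so the document does not show that it is wrong.

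**Conclusion.** The inconsistency is real and should be corrected. The hold threshold for skin toxicity conflicts with the restart condition and with the counted grade 3 steps in the same paragraph, and a first grade 3 event is left without a mandated hold. Grade ≥ 3 is the reading that makes the paragraph coherent. That it was the intent is an inference from the surrounding steps, though a strong one.

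The consequence is confined to treatment and safety rules. The two-stage design with 14 and 34 patients, its power and type I error, and the definition of response are unaffected. The 26% rate, assumed to carry over from another trial, shows only that the rule concerns a common toxicity of the study drug and would be used in practice.

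**What to change.** Change the hold trigger to grade ≥ 3 cutaneous toxicity and, for consistency, write grade ≥ 3 in the later skin steps as well. The ladder then reads:

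1. First event: 2-week delay, restart at grade 2 or lower.
2. Second event: 2-week delay, then 200 mg/mq.
3. Third event: 2-week delay, then 150 mg/mq.
4. Fourth event: permanent discontinuation.

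The existing 4-week suspension rule stays as it is. Using grade ≥ 3 throughout also settles the restart dose after a recurrent grade 4 event. If the sponsor prefers a stricter rule for grade 4, that is a clinical choice to be stated at this point.

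The cost is a correction of a few symbols in one paragraph. Sample size, endpoints, visits and analyses do not change.

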### Response and toxicity assessment

The assessment of response will be perfomed through total-body computed tomography with iv contrast (if contraindicated: abdomen MRI and chest computed tomography without iv contrast), CEA and CA19.9 after 3 months of folfiri/cetuximab and every 3 months thereafter until progression. Responses will be classified according to the RECIST v. 1.1. An independent blinded central review of radiologic examinations will be performed by a DMC (Data Monitoring Committee). The independent DMC will be also responsible of reviewing the PFS data. Toxicity will be assessed in accordance with the CTCAE, version 4.0. The CTCAE contains 26 categories of adverse events, organized for pathophysiology, anatomy and etiology. Each adverse event is graded with a scale ranging from 0 (absence of event or value within the normal range) to 5 (death caused by the adverse event). Patients will be assessed for the presence of adverse events at each study visit and will also notify the investigator by telephone in case of significant adverse events reported between one visit and the next. For each adverse event, the maximum grade per patient will be reported. If a patient experiences a toxic effect of any grade on multiple occasions, the event will be counted only once.

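### The first cetuximab hold for skin toxicity is triggered above grade 3, but the later steps assume that a first grade 3 event was already held

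*Protocol article*

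**What the plan says.** The skin-toxicity rules for cetuximab stand in one paragraph of the Protocol article, under Dose modifications for cetuximab.

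- First step: "Cetuximab infusion will be delayed in case of grade > 3 cutaneous toxicity for 2 weeks".
- Restart: "The treatment will be reintroduced if the cutaneous toxicity reduces to grade 2 or lower".
- Second and third steps: "If grade 3 skin toxicity reoccurs at a second or third time, cetuximab will be postponed for a further 2 weeks", and then "but when reintroduced the dose will be reduced to 200 mg/mq and 150 mg/mq, respectively".
- Stop: "it will be permanently discontinued in case of 4 weeks suspension or fourth grade 3 toxicity event occurrence despite appropriate dose adjustments".

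Three other sections bear on how to read this. Response and toxicity assessment gives the scale: "Each adverse event is graded with a scale ranging from 0 (absence of event or value within the normal range) to 5", with 5 meaning death. Dose modifications for folfiri uses an inclusive threshold, for example "At the second appearance of grade ≥ 3 side effects a dose reduction of 50% will be applied". Duration of therapy has a general exit without a grade: "In case of unacceptable toxicity related to cetuximab the patient will continue folfiri until progression". The weekly cetuximab dose after loading is 250 mg/m² (Therapeutic schedule).

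**The concern.** The opening threshold and the steps that follow it do not fit together. The recurrence sentence speaks of grade 3 toxicity coming back and of an additional 2-week postponement. That presupposes an earlier postponement for grade 3, but the only earlier one in the paragraph excludes grade 3 by its wording.

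Two gaps follow for anyone applying the text literally. At a first grade 3 skin reaction there is no instruction to hold cetuximab. At a recurrent grade 4 reaction the rule is less complete than at a recurrent grade 3 reaction, although the event is worse.

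What is at stake is patient safety and consistent cetuximab exposure in a single-arm trial of that drug. The Simon two-stage boundaries and the primary analysis are not affected.

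**Working it through.** The plan gives no figure to reproduce here. The check is to follow the rules event by event and compare them with an inclusive threshold.

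**Step 1: what the opening trigger covers.** On a 0 to 5 scale, above grade 3 means grades 4 and 5. Grade 5 is death, so in practice the first hold applies to grade 4 only.

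**Step 2: whether another section fills the gap at grade 3.** None does. Duration of therapy relies on unacceptable toxicity without defining it by grade. Dose modifications for folfiri governs the chemotherapy, not cetuximab. End-of-treatment phase deals with following skin toxicity after treatment has ended.

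**Step 3: the sequence as written against grade ≥ 3 at every step.** Doses are those given on restart, in mg/m². As written, a repeated grade 4 event meets only the opening sentence, plus the stop after 4 weeks of suspension.

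| Skin event | Grade 3 each time, as written | Grade 4 each time, as written | Either grade, with ≥ 3 throughout |
|---|---|---|---|
| 1st | no hold stated; 250 | delay; 250 | delay; 250 |
| 2nd | delay; 200 | delay; no reduction stated (250) | delay; 200 |
| 3rd | delay; 150 | delay; no reduction stated (250) | delay; 150 |
| 4th | permanent stop | delay; no stop on event count | permanent stop |

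**Step 4: size of the differences.**

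- Grade 3 sequence: 1 of 4 steps differs, the first. A 2-week hold of a weekly dose withholds 2 × 250 = 500 mg/m², against none.
- Grade 4 sequence: 3 of 4 steps differ. At the second event the dose is 250 rather than 200, and 1 − 200/250 = 20%. At the third it is 250 rather than 150, and 1 − 150/250 = 40%. At the fourth it is a delay rather than a permanent stop.
- Mixed sequence, grade 4 and then grade 3: the text does not settle whether the grade 3 event is the first or the second step. The restart dose could be 250 or 200 mg/m².

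**Step 5: how many patients could meet these rules.** The article does not separate grade 3 from grade 4 skin reactions and gives no recurrence rates, so the number affected cannot be derived. For orientation only, the Background reports 26% grade 3–4 skin reactions with folfiri plus cetuximab in a cited phase III first-line study. If that rate held here, which is an assumption, 0.26 × 34 = 8.8, or about 9 of the 34 planned patients, would have such a reaction. That is roughly an upper limit for the first-hold gap under this assumption, not an estimate of patients treated wrongly.

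**The case against.** The strongest reply is that the paragraph corrects itself. Restart at grade 2 or lower, the reference to recurrence, the additional 2 weeks and the count up to a fourth grade 3 event all point to an inclusive first threshold. An experienced oncologist would probably hold cetuximab at a first grade 3 reaction. Nor would a clinician readily read a rule for grade 3 as sparing a grade 4 reaction. The grade 4 comparison also needs four separate grade 4 events, each recovering in time, with nobody calling the toxicity unacceptable. These points stand as limits on the practical harm. They do not make the stated threshold correct.

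A second reply is that the sign was altered in typesetting or conversion, or that the full protocol, which is not shown, has it right. Neither can be excluded. However, the folfiri section directly before prints ≥ intact, and nothing in the text points to a lost character. The article also sets out the whole sequence with grades, delays, doses and a stop. The issue is therefore a stated threshold that its own paragraph contradicts, not detail left to a fuller document.

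A third reply is that the same paragraph uses the same sign for allergic reactions, which a correction of the skin rule leaves untouched. That is true, but it is a separate point and does not weaken this one.

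**Conclusion.** The concern holds. The first skin-toxicity threshold for cetuximab is wrong as written, because it contradicts the recurrence and stop rules in the same paragraph. Literally applied, it leaves out the hold at a first grade 3 event (about 500 mg/m² not withheld). It also gives repeated grade 4 events no stated dose reduction and no stop on event count.

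This rests on a literal reading of the printed sign and of grade 3 as grade 3 only. The intended meaning is very probably grade 3 or higher. The matter is a minor-to-moderate safety wording correction. The number of patients affected cannot be stated from the document, and the sample size and primary test do not change.

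**What to change.** In Dose modifications for cetuximab, write grade ≥ 3 in three places:

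1. the opening trigger for the 2-week delay;
2. the recurrence step that leads to 200 and then 150 mg/m²;
3. the fourth-event permanent stop.

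Keep the restart condition (grade 2 or lower) and the stop after 4 weeks of suspension. Grade 4 is then handled at least as strictly as grade 3, and the sponsor may set a stricter rule for grade 4. The sign in the allergic-reaction rule of the same paragraph can be confirmed at the same time.

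The cost is a wording change in one paragraph, with no added patients or procedures.
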